### Sample size calculation

The sample size was calculated assuming a 1:1 randomization ratio, a two-sided type I error rate (α) of 0.05, and 80% statistical power to detect a hazard ratio of 0.5 between the NAC and placebo groups, based on an estimated 33.3% baseline probability of disease progression among pregnant women with early-onset preeclampsia [24]. Allowing for an anticipated 15% loss to follow-up or missing outcome data, the total planned sample size is 153 participants, who will be randomly allocated in equal proportions to the two study arms (approximately 76–77 participants per group).

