## Discussion

Preeclampsia is a multisystem hypertensive disorder of pregnancy occurring after 20 weeks’ gestation [1] and affects about 2–8% of pregnancies globally [2], with a higher burden in Nigeria [3]. It remains a major cause of maternal and perinatal morbidity and mortality, particularly in low-resource settings [4]. Preeclampsia with severe features is associated with significant complications, including organ dysfunction and adverse fetal outcomes [2,5]. Despite advances in care, prevention of disease progression remains limited. Current strategies such as low-dose aspirin offer partial benefit, while delivery, the only definitive cure, often leads to preterm birth [8]. Therefore, there is a critical need for effective therapies that can delay progression to severe disease and improve outcomes. Oxidative stress and inflammation are key mechanisms in the pathogenesis of preeclampsia [10]. NAC, an antioxidant and glutathione precursor, has demonstrated anti-inflammatory and vasodilatory effects, making it a promising candidate for repurposing [11]. Preliminary studies suggest NAC may reduce oxidative stress and disease progression [12–15]; however, robust evidence from well-powered randomized controlled trials is lacking. This protocol, therefore, describes a proof-of-concept double-blind, randomized, controlled trial to be conducted in the maternity units of two hospitals in Lagos, Nigeria, between April 2026 and July 2028 to evaluate whether NAC can delay progression to preeclampsia with severe features in women with early-onset preeclampsia. We have powered the study to detect the primary outcome that pregnant women aged 18 years or older with early-onset preeclampsia who had treatment with NAC will achieve delayed progression to severe disease. Therefore, if effective, NAC could offer a safe, affordable, and scalable intervention to reduce the burden of preeclampsia, particularly in resource-constrained settings.

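### The stated inputs (HR 0.5, 33.3% baseline progression, 15% loss) do not give 153 participants at 80% power; they give about 52–59%, so the 33.3% and the 153 must be reconciled

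*Protocol article*

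**What the plan says.** The Sample size calculation section of the protocol article gives a full set of inputs and a result:

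- allocation: "The sample size was calculated assuming a 1:1 randomization ratio"
- type I error: "a two-sided type I error rate (α) of 0.05"
- power and effect: "80% statistical power to detect a hazard ratio of 0.5 between the NAC and placebo groups, based on an estimated 33.3% baseline probability"
- event probability: "based on an estimated 33.3% baseline probability of disease progression among pregnant women with early-onset preeclampsia"
- loss to follow-up or missing outcome: 15%
- result: "the total planned sample size is 153 participants"

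No number of events and no formula are given. The section on data management and statistical considerations names the log-rank test for the primary endpoint, followed by a Cox model. The Discussion repeats the claim: "We have powered the study to detect the primary outcome".

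**The concern.** The power of a log-rank test depends on the number of events, not on the number of women. If a third of the placebo arm progresses and the hazard is halved on NAC, only about a quarter of all women will have an event. A quarter of 130 to 153 women is roughly half of what a hazard ratio of 0.5 requires at 80% power.

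The Introduction and the Discussion both justify the trial by the lack of well-powered randomised evidence. If the 33.3% is right, a non-significant result would be read as evidence against NAC from a trial described as adequately powered, although that trial would have had little better than an even chance of detecting its own target effect.

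**Working it through.** **Inputs** (all from Sample size calculation): 1:1 allocation; two-sided alpha 0.05 (z = 1.960); power 80% (z = 0.8416); HR 0.5; placebo progression 0.333; loss 15%; N = 153.

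**1. Events required.** (1.960 + 0.8416)² = 7.849.
- Schoenfeld: 4 × 7.849 / (ln 0.5)² = 65.3, so 66.
- Freedman: 7.849 × [(1 + 0.5)/(1 − 0.5)]² = 7.849 × 9 = 70.6, so 71.

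**2. Event probability.** Under proportional hazards, NAC progression = 1 − (1 − 0.333)^0.5 = 0.183. The mean of the two arms is (0.333 + 0.183)/2 = 0.258.

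**3. Can 153 be reproduced as stated?** N = events / 0.258, then divided by 0.85.
- Schoenfeld: 66 / 0.2581 = 256 evaluable, about 301 enrolled (298 with unrounded events).
- Freedman: 71 / 0.2581 = 275 evaluable, about 324 enrolled.

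Other two-sided readings, each with 15% loss, also miss 153:
- 33.3% applied to both arms: 233 (Schoenfeld) or 251 (Freedman)
- NAC risk simply halved to 16.65%: 311 or 335
- comparison of two proportions: 248 to 346

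**4. Power that the stated inputs give.** Schoenfeld power = Φ(0.693 × √events / 2 − 1.960); Freedman power = Φ(√events / 3 − 1.960). After 15% loss, 153 × 0.85 = 130.

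| Women contributing | Events | Schoenfeld | Freedman |
|---|---|---|---|
| 130 (after 15% loss) | 130 × 0.2581 = 33.6 | 52% | 49% |
| 153 (no loss) | 153 × 0.2581 = 39.5 | 59% | 55% |
| 130, with 33.3% as the rate in both arms | 43.3 | 63% | 59% |
| 153, with 33.3% as the rate in both arms | 50.9 | 70% | 66% |

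The last row is the most generous two-sided reading. It makes two concessions that the text does not.

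**5. Effect detectable with 80% power (Schoenfeld).** NAC events fall as the HR falls, so the HR is solved together with its own event count.
- 130 women: HR 0.36, NAC progression 1 − 0.667^0.363 = 13.7%, 30.5 events.
- 153 women: HR 0.40, NAC progression 1 − 0.667^0.397 = 14.9%, 36.8 events.

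Holding events at 33.6 would give 0.38, but at that HR NAC progression is 14.3%, events are 30.9 and power is 77%.

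**6. An input that does give 153.** Take 0.333 as the placebo probability of staying progression-free, so that 66.7% progress. The NAC progression-free probability is 0.333^0.5 = 0.577. Freedman: N = 2 × 70.64 / (2 − 0.333 − 0.577) = 129.6, rounded up to 130. Then 130 / 0.85 = 152.9, rounded up to 153. Expected events are 130 × 0.545 = 70.8, about 71, with power 80% (Freedman) or 83% (Schoenfeld).

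**The case against.** The strongest objection is that the trial may be correctly sized and only the sentence wrong. If 66.7% progression was intended, 153 delivers its 80%, and printing 52% would replace a true statement with a false one. This stands. It is why the input must be settled before the power is restated.

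Second, 52% is a pessimistic figure, because women lost to follow-up still contribute time and events until they are censored. This also stands, and the range 52–59% allows for it.

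Third, the composite in Study outcomes is broad (blood pressure, proteinuria, laboratory, symptom and placental criteria), so actual progression could exceed 33.3%. That is possible, but the article states 33.3% and argues for no other figure.

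Fourth, other inputs also come close to 153. An overall event probability of 50% gives 65.3 / 0.50 / 0.85 = 153.8, so 154. A one-sided test with 33.3% in both arms and no loss gives 51.5 / 0.333 = 154.6. The first uses a figure that the article does not state; the second contradicts its two-sided alpha and its 15% loss. Neither gives 153 exactly.

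Fifth, an article may leave the formula and the event count to a fuller document. That is fair, and their absence is not the finding. The finding is that the printed inputs and the printed result disagree.

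A reader might go further and infer that the trial is underpowered, or that the complement was certainly entered by mistake. The article supports neither. The 52–59% depends on 33.3% progression being right, and the match in step 6 is an inference from arithmetic.

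**Conclusion.** The statement is wrong as written: 33.3% progression and 153 participants at 80% power cannot both be right with the other stated inputs. On those inputs power at HR 0.5 is about 52–59% by Schoenfeld (49–55% by Freedman), from about 34 to 40 events against 66 or 71 needed, and 80% would take about 300–324 enrolled. No two-sided reading with 33.3% as a progression probability exceeds about 70%.

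These figures assume proportional hazards and 33.3% as the placebo probability over follow-up. They ignore the two planned interim analyses for efficacy and futility. The source cited for the 33.3% is not at hand, so whether the wording or the calculation slipped cannot be decided from the article.

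**What to change.** Reconcile the 33.3% with the 153, and state in Sample size calculation the placebo progression probability that was actually used.

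- If about 66.7% progression was intended, replace 33.3% with that figure and justify it. The 153 and the 80% then stand, with about 71 events.
- If 33.3% progression is intended, keep 153 and restate the section: about 34–40 expected events; about 52–59% power at HR 0.5; 80% power only at an HR of about 0.36 with 130 evaluable women, or about 0.40 if all 153 contribute fully. Align the Discussion's claim that the study is powered. Retaining 80% at HR 0.5 would instead mean enrolling about 300–324 women.

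The first route costs wording and a justification. The second also costs wording only, with no extra participants if 153 is kept, but the stated power becomes less favourable. According to Trial status, recruitment had not begun at submission, so either correction could be made before any outcome data exist.

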### Study procedures

The study team will screen and enrol n = 153 consecutively consenting pregnant women diagnosed with early-onset preeclampsia during their routine antenatal care or at the maternity units of the participating hospitals. We will enrol approximately 40% of participants at LUTH (n = 61) and 60% at LIMH (n = 92), reflecting differences in patient volume and prior recruitment performance. Once the study intent and procedures are introduced and informed consent obtained, baseline sociodemographic, obstetric, dietary, and laboratory (haemoglobin, liver function tests, kidney function tests, glutathione, and homocysteine status) information will be collected using an electronic case report form (CRF) on REDCap. A baseline ultrasound scan assessment will be done and documented. Gestational age is based on the date of the participant’s last menstrual period, which will be obtained at the time of random assignment or calculated from the baseline ultrasound biometry. Body mass index (BMI) is obtained by dividing the actual maternal weight (calculated by subtracting the estimated fetal weight at enrolment using a normogram chart from the measured maternal weight) by the maternal height (in kg/m^2^).

### Randomization and allocation concealment

Participants will be randomly assigned using a 1:1 block random sequence of 4–6 blocks generated by the study statistician from Random Allocation software version 1.0 (May 2004) prepared in advance of the trial to receive either a daily oral tablet containing 600 mg of NAC or a placebo tablet to match the NAC tablets in size, shape, colour, and overall appearance to maintain blinding in addition to standard antenatal care from diagnosis (randomisation) until either 34 weeks’ gestation or delivery, whichever comes first [Fig 1]. The active drug (NAC) and placebo tablets will be packed in identical, coded, transparent dispensing sachets by the onsite pharmacy technician. The technician will then store the coded randomisation list in a sealed, opaque envelope, which will be kept in a locked file cabinet at the study site until the end of the study. The 600 mg oral daily dosage of NAC was selected after a careful review of the literature on the effectiveness of NAC in exerting antioxidant, anti-inflammatory, and antiproliferative effects while maintaining a favourable safety profile [16–21]. Furthermore, a low dose of 600 mg daily aligns with widely available commercial formulations that offer better gastrointestinal tolerability, which is important for sustained adherence in our study population and will also simplify procurement and ensure consistent dosing during the study. The placebo tablets will be composed of inert excipients, including microcrystalline cellulose, lactose, and magnesium stearate, and will contain no active pharmacological ingredient. Given the characteristic sulfur-like odour and taste of NAC, both NAC and placebo tablets will be administered with Coca-Cola Zero Sugar immediately prior to ingestion to mask any sensory differences and minimize the risk of unblinding. Participants, investigators, and outcome assessors will remain blinded to treatment allocation throughout the study period. To evaluate the effectiveness of blinding, a blinding assessment will be conducted at the end of the intervention period. Participants and study personnel will be asked to indicate their perceived treatment allocation (NAC, placebo, or unsure). The success of blinding will be assessed by comparing the distribution of guesses between groups against that expected by chance. All study participants, irrespective of treatment arm allocation, will receive standard-of-care management for early-onset preeclampsia in accordance with the institutional protocol and internationally accepted guidelines. The study intervention will only be administered as an adjunct to standard care, which will include corticosteroids for fetal lung maturation, antihypertensive treatment, magnesium sulphate for seizure prophylaxis (when indicated), close maternal and fetal monitoring, and delivery based on standard clinical indications.

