### Data management and statistical considerations

Data will be collected prospectively with continuous data entry and checking. Queries will be actively pursued to ensure prompt clarification. Data will be entered into the REDCap database and then exported to Stata version 18.0 for Windows (StataCorp LLC, Texas, USA) for statistical analyses. Missing or incomplete data will be handled by running a missing values analysis using pairwise or listwise deletion if no pattern is detected or the multiple imputation method if a pattern is detected [26]. The primary analysis will be conducted on an intention-to-treat basis. The effectiveness of blinding will be evaluated using descriptive statistics and by comparing the proportion of correct guesses between study arms using the Chi-square test. Kaplan-Meier estimates with a Log-rank test will be used to calculate and compare the time-to-disease progression for the treatment groups while considering deliveries without preeclampsia with severe features as censored observations. We will then perform Cox proportional hazard models with a backwards conditional method to compare the study outcomes between the treatment arms while adjusting for other covariates using hazard ratios (HRs) and 95% confidence intervals (95%CIs). We will assess the calibration or goodness-of-fit statistic of the final model using the Hosmer-Lemeshow test, while the model’s explanatory power will be reported with Nagelkerke’s pseudo-R². Subgroup analyses will also be performed to assess the differential effects of significant covariates on the impact of NAC on disease progression. With oversight from the DSMC, two interim analyses of efficacy and futility for the primary outcome (progression to severe disease) will be conducted at 50% and 75% enrolment using O’Brien-Fleming stopping criteria [27] at cutoff *p*-values of less than 0.013 and 0.025, respectively

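### Neither the block randomisation nor the stated log-rank and Cox analyses name hospital as a stratum in a two-hospital trial: a minor, cheaply mended gap in balance and precision

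*Protocol article*

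**What the plan says.** The protocol article's section on randomization and allocation concealment gives the mechanics in some detail: "Participants will be randomly assigned using a 1:1 block random sequence", with 4–6 given for the blocks and the study statistician as its source. It also names the software and says that the coded list is "kept in a locked file cabinet at the study site until the end of the study". It mentions no stratification factor, and it does not say whether there is one list for the trial or one per hospital.

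The section on study procedures sets the split between hospitals: "We will enrol approximately 40% of participants at LUTH (n = 61) and 60% at LIMH (n = 92"). The reason given is "reflecting differences in patient volume and prior recruitment performance". These are targets, not fixed quotas.

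The section on data management and statistical considerations gives the comparison of arms: "Kaplan-Meier estimates with a Log-rank test will be used to calculate and compare the time-to-disease progression for the treatment groups". No strata are named. It continues with "Cox proportional hazard models with a backwards conditional method to compare the study outcomes between the treatment arms while adjusting for other covariates". Hospital is neither listed as a covariate nor protected from elimination.

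**The concern.** Hospital is known for every woman at randomisation and could plausibly be prognostic. Standard care follows institutional protocol, and the composite endpoint includes clinically judged and ultrasound components. Blocks that run across two hospitals balance the overall total but not the arms within each hospital. An analysis that ignores hospital then neither corrects a chance imbalance nor uses the information that hospital carries.

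What goes wrong depends on how the lists are held. With one common list, the risk is imbalance within hospital and some loss of precision. With one list per hospital, the randomisation is in effect stratified but the test ignores the strata and becomes conservative. The two consequences exclude each other, and the article does not say which applies.

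**Working it through.** **Inputs from the protocol article.** Total 153, 1:1; hospital targets 61 and 92; "a two-sided type I error rate (α) of 0.05, and 80% statistical power to detect a hazard ratio of 0.5"; 33.3% baseline progression risk; 15% loss. The block wording is read as block sizes 4 and 6.

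**Assumed, because the documents give no figure.** Hazard ratio between hospitals of 1 to 3; exponential times. The plan states nothing on balance within hospital, so it has no figure of its own to reproduce.

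**1. Balance within the smaller hospital under one common list.** If women arrive from the two hospitals in random order, the number A allocated to NAC among the 61 is close to hypergeometric (taking 77 of 153 on one arm):

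- Var(A) = 61 × (77/153) × (76/153) × (92/152) = 9.23, so SD(A) = 3.04.
- The arm difference is 2A − 61, with SD 2 × 3.04 = 6.1. Simulation of the block sequence (20,000 runs) also gave 6.1.
- A difference of 11 or more means A ≤ 25 or A ≥ 36. With continuity correction z = 5/3.04 = 1.645, so the two-sided probability is 0.10. Simulation gave 10%.
- A difference of 9 or more (35 v 26): z = 4/3.04 = 1.32, probability 0.19. Simulation gave 19%.
- With a separate list per hospital, the simulated difference never exceeded 3.

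**2. What such an imbalance does to one trial's estimate.** Take 36 v 25 in the smaller hospital and 40 v 52 in the larger, with no drug effect. If the smaller hospital's hazard is twice the other's, the unadjusted initial hazard ratio is [(36×2 + 40)/76] ÷ [(25×2 + 52)/77] = (112/76)/(102/77) = 1.11. At three times it is (148/76)/(127/77) = 1.18. This is a chance shift in a single trial. It averages out over repetitions.

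**3. Expected events.** With hazard ratio 0.5 the NAC risk is 1 − (1 − 0.333)^0.5 = 0.183, so the average risk is (0.333 + 0.183)/2 = 0.258. Then 153 × 0.258 = 39.5 events with no loss. If the 15% are lost evenly over follow-up, this is about 39.5 × 0.925 = 37.

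**4. Power at hazard ratio 0.5 and 33.3% placebo risk.** Each cell compares one list with a plain log-rank test against lists per hospital with a stratified log-rank test.

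| Hospital hazard ratio (assumed) | 15% loss, 2,000 runs | No loss, 4,000 runs |
|---|---|---|
| 1 | 54% v 54% | 57.4% v 57.2% |
| 1.5 | not run | 57.0% v 57.6% |
| 2 | 52% v 53% | 56.4% v 57.0% |
| 3 | 49% v 54% | 52.8% v 56.8% |

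Simulation error is about ±2 points with 2,000 runs and about ±1.5 with 4,000. Up to a hospital hazard ratio of 2 the differences lie within it. At 3 these two runs give 4 and 5 points, and a further check put the gain as low as about 2. Larger losses need a much higher event risk than the plan states: at an assumed 66.7% placebo risk, 86.2% v 87.6% at 2 and 81.0% v 88.2% at 3.

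**5. Which half of the change does the work.** At 33.3% risk and hospital hazard ratio 3 (no loss), one list with a stratified test gives 56.8%, the same as lists per hospital with a stratified test. Lists per hospital with a plain test give 53.8%. The stratified analysis recovers the power; the stratified lists secure the balance.

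**6. Type I error (nominal 5%).** One list with a plain test: 4.4% to 5.4% in all scenarios. Lists per hospital with a plain test at hospital hazard ratio 3: 3.9% at 33.3% risk and 3.0% at 66.7%.

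**The case against.** The strongest objection is that a single common list is only inferred. The article speaks of an onsite technician and, in the follow-up text, of technicians in the plural, which fits one list per hospital. It is also a condensed account, and the full protocol or analysis plan may name hospital as a stratum. This stands, and so the point is put for both readings. It does not remove the point: the randomisation paragraph is detailed enough that a stratification factor would be expected there, and the analysis section states a test without strata.

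The second objection is that nothing shows that the hospitals differ in progression risk. Eligibility, endpoint definition, training and operating procedures are common to both, and care also follows international guidelines. The unequal targets reflect volume and recruitment, not risk. This stands too: every power figure above depends on an assumed hospital effect, and at the stated risk the gain is invisible unless that effect is large.

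A reader might infer that chance imbalance biases the trial or inflates false positives. The calculations do not support that: the plain test keeps its level, and the imbalance is part of ordinary sampling variation. A reader might also infer that precision will certainly be lost, or that 61 and 92 are quotas. The documents support neither.

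**Conclusion.** The point holds as a minor improvement. The article names hospital in neither the randomisation nor the analysis, and under either reading of how the lists are held a slightly better method is available. With one list, a difference of 11 or more among 61 women arises in about 10% of trials; the power at stake is negligible up to a hospital hazard ratio of 2 and about 2 to 5 points at 3. With a list per hospital, the plain test runs at about 3 to 4% instead of 5% at a hospital hazard ratio of 3. The imbalance figure rests only on the stated targets, random arrival order and a common list. The power and type I error figures rest on hospital effects that are assumed. Nothing here invalidates the trial. The simulated power of roughly 50 to 57% at the stated 33.3% risk, against the planned 80%, is a separate matter that stratification would not repair.

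**What to change.** - **Randomization and allocation concealment:** state that a separate permuted-block list is generated for each hospital, and for any recruitment site added later, with block sizes 4 and 6 in random order.
- **Data management and statistical considerations:** make the primary log-rank test and the Cox model stratified by hospital, and say that hospital is not subject to backward elimination.

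The cost is one sentence in each section and two lists instead of one from the same software. If the hospitals do not differ, simulation puts the loss at no more than about 1 point of power. The sample size does not change. The timing matters for the first item: recruitment had not begun when the article was submitted, and balance within hospital cannot be restored once women are randomised. The analysis change can be made later, but should be fixed before any unblinded look at the data.
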